### Primary outcomes

The primary outcomes are the incidence of PPCs (diagnostic criteria shown in Tables 3 and 4) and perioperative mortality rate.

**Table 3 Tab3:** Classifications of PPCs

Grading	Definition
0	No pulmonary complications
1	Any one of the following: cough, minor lung atelectasis (no obvious cause), dyspnea (no obvious cause)
2	Cough and sputum production (no obvious cause), bronchospasm (new-onset asthma or exacerbation of existing asthma that requires treatment), hypoxemia (SpO2 < 90% or PaO2 < 60 mmHg while breathing air), atelectasis (diagnosed by radiography or abnormal pulmonary sign with T > 37.5), hypercapnia (temporary or requires treatment; caused by medication or over-ventilation)
3	Pleural effusion (that requires drainage), suspected pneumonia (indicated by radiography, with or without microbiologic findings), diagnosed pneumonia (diagnosed based on the combination of radiology finding and microbiology evidence such as Gram staining or culture), pneumothorax (suggested by X-ray: observation of a lucent gas space devoid of pulmonary vessels between visceral pleura and the parietal pleura or symptoms of dyspnea, chest pain, irritating cough), noninvasive or invasive mechanical ventilation < 48 h
4	Respiratory failure (that requires noninvasive or invasive mechanical ventilation for > 48 h)

*PaO2* partial pressure of oxygen, *SpO2* blood oxygen saturation, *T* body temperature

**Table 4 Tab4:** Definition of PPCs

Complications	Diagnostic criteria
Pneumonia	X-ray finding of a new or progressive pulmonary infiltration and meeting 2 of the following 3 indications:
	(1) Cough, exacerbation of dyspnea or purulent sputum
	(2) Body temperature above 38 °C or under 36 °C
	(3) WBC > 12,000 or < 4000/μL
Atelectasis	Mainly based on X-ray findings as follows:
	Lung collapse
	Compensatory hyperinflation of adjacent ipsilateral lung tissue
	Wedge- or linear-shaped opacities
	Shifting of mediastinum
	Diaphragm move towards the collapse
Pleural effusion	X-ray finding of obscure or disappearance of costophrenic angle, obscured ipsilateral diaphragm
SIRS	(1) Core body temperature > 38 °C or < 36 °C
	(2) HR > 90 bpm, in cases of atrial arrhythmia, ventricular rate > 90 bpm; exclude when used medications that may affect heart rate
	(3) RR > 20 bpm, or PaCO2 < 32 mmHg (4.2 kPa), or urgent mechanical ventilation used
	(4) WBC > 12,000 or < 4000/μL

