## Statistics and data analysis

### Sample size estimations

Power Analysis and Sample Size (PASS) software (version 11.0; Number Cruncher Statistical Software (NCSS), LLC, Kaysville, UT, USA) was used for the sample size calculation. The χ^2^ test for a multiple proportions procedure was used. With an α = 0.05, a power of 90%, an effect size = 0.09, and degrees of freedom = 2, we estimated that 2584 patients would be required for our study. If the attrition rate was set at 10%, a total of 6000 patients (3000 in each group) would be required. The effect size was calculated from the assumption that the LMA would cause a reduction from 15% to 10% for the incidence of PPCs. The incidence of PPCs for patients undergoing different types of surgeries has been reported to be in the range of 1–23% [5]. Therefore, a proportion of 10% of the patients in the LMA group were expected to develop PPCs, and this was used to calculate the sample size.

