### Statistical analysis

Statistical analyses will be performed by an independent statistician using SAS 9.4 software (SAS Institute Inc., Cary, NC, USA). After normality testing, the patients’ data will be presented as the mean and standard deviation (SD) if they are normally distributed; otherwise, they will be presented as the mean and interquartile range. To compare numerical data, a paired or an unpaired *t* test will be used for normally distributed data, and the Kruskal-Wallis test will be used for skewed data. The χ^2^ test and Fisher’s exact test will be used to compare proportional data. When two χ^2^ tests are performed, the *P* value is adjusted to 0.025. A *P* value < 0.05 will be considered statistically significant. If *P* < 0.05, the Nemenyi test will be used to compare the difference between two groups. A logistic regression model will be developed to detect any potential confounding factors.

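### The significance threshold for the two primary outcomes is not fixed unambiguously: 0.025 in one sentence, 0.05 in the next and in the sample size

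*Protocol article*

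**What the plan says.** The Primary outcomes section of the protocol article states: "The primary outcomes are the incidence of PPCs (diagnostic criteria shown in Tables 3 and 4) and perioperative mortality rate". Both are proportions, and for these the Statistical analysis section provides: "The χ^2^ test and Fisher’s exact test will be used to compare proportional data".

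Two consecutive sentences in the same section then set thresholds. The first is conditional on a pair of χ² tests being carried out; the second carries no condition. Across the two, the text reads: "value is adjusted to 0.025. A *P* value < 0.05 will be considered statistically significant".

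The sentence that follows takes 0.05 as the gate to a further step, in which "the Nemenyi test will be used to compare the difference between two groups".

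The Sample size estimations section begins its inputs "With an α = 0.05, a power of 90" (per cent). It rests on a fall in PPC incidence from 15% to 10%, and gives no mortality rate, difference or power.

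**The concern.** The 0.025 sentence looks like a multiplicity adjustment, but it does not say which two tests it covers. Several secondary outcomes are also proportions (ICU admission and re-admission, for example), so the number of χ² tests does not single out the two primary outcomes. Read literally, the condition would not even be met if one primary outcome were tested by Fisher's exact test. The sentence after it calls P < 0.05 significant without an exception, and the sample size uses 0.05 as well.

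What is at stake is how a primary P value of, say, 0.03 is read. Two readers could reach opposite conclusions from the same page. If the choice is made once results are known, it cannot be defended as pre-specified. If 0.05 is used for both outcomes and either can carry the claim, the chance of a false claim is nearly double the nominal 5%.

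**Working it through.** **1. The plan's own sample-size figure.** The stated inputs are α = 0.05, power 90%, effect size w = 0.09 and 2 degrees of freedom. The noncentrality needed is 12.654, so N = 12.654 / 0.09² ≈ 1563. The article gives 2584, so its figure does not reproduce. That is a separate matter, and nothing below depends on 2584.

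**2. Where each threshold appears.**

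| Place | Threshold | Tied to the primary outcomes? |
|---|---|---|
| Statistical analysis, two χ² tests | 0.025 | Not by name |
| Statistical analysis, general rule | 0.05 | No exception given |
| Statistical analysis, gate to Nemenyi test | 0.05 | No |
| Sample size estimations | 0.05 | Yes, PPC incidence |

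**3. Family-wise error if either primary outcome can support a claim.**

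- 0.05 each: 1 − (1 − 0.05)² = 0.0975 if independent; upper bound 2 × 0.05 = 0.10.
- 0.025 each: 1 − (1 − 0.025)² = 0.0494 if independent; upper bound 2 × 0.025 = 0.05.

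**4. What 0.025 costs for PPC incidence.** Inputs: 15% versus 10% and 1:1 allocation (article); 3000 per group less 10% attrition = 2700 evaluable per arm.

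- Standard error under no difference: √(2 × 0.125 × 0.875 / 2700) = 0.00900.
- Standard error under 15% versus 10%: √((0.15 × 0.85 + 0.10 × 0.90) / 2700) = 0.00898.
- Power at 0.05: Φ((0.05 − 1.960 × 0.00900) / 0.00898) = Φ(3.61) = 99.98%.
- Power at 0.025: Φ((0.05 − 2.241 × 0.00900) / 0.00898) = Φ(3.32) = 99.96%.

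For 90% power the same method needs 918 per arm at 0.05 (1836 in total; 1836 / 0.9 = 2040 with attrition). At 0.025 it needs 1084 per arm (2168 in total; 2168 / 0.9 ≈ 2409). Both are far below 6000.

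**5. Which PPC results fall in the disputed zone.** With a pooled incidence of 12.5% (the midpoint of 15% and 10%), P lies between 0.025 and 0.05 when the observed difference is between 1.960 × 0.00900 = 1.8 and 2.241 × 0.00900 = 2.0 percentage points. If the planned 5-point difference is true, such a result is very unlikely (99.98% − 99.96% = about 0.02%). The zone matters if the true effect is much smaller, and for mortality.

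**6. Mortality.** The article gives no rate, so the control rates and the halving here are assumptions. There are 2700 patients per arm.

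| Assumed control mortality | Power at 0.025 | Power at 0.05 |
|---|---|---|
| 0.5% | 23% | 32% |
| 1% | 46% | 57% |
| 2% | 78% | 86% |
| 3% | 93% | 96% |

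**The case against.** The strongest reply is that the sentences can be reconciled. The 0.025 sentence is conditional, there are exactly two primary outcomes, and both are proportions. The natural reading is a Bonferroni split for those two, with 0.05 as the default elsewhere, and the family-wise error is then 4.94%. This reply largely stands. A reader might infer that the plan flatly contradicts itself, or that it runs a 9.75% false-positive risk. The text does not support either: 9.75% arises only if the 0.025 sentence is set aside. What survives is that the article never states the charitable reading, and that neither the unqualified 0.05 sentence nor the sample-size α fits it.

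A reader might also infer that the rule for a positive trial is defective. The article states no rule on whether one or both primary outcomes must succeed. That rule may properly sit in the analysis plan, so its absence is not part of this point.

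A third tempting inference is that the trial is underpowered for mortality. The figures do not show this. They rest wholly on assumed rates and run from 23% to 93% at 0.025. Sizing a trial on one of two primary outcomes is not an error in itself.

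Finally, the Nemenyi sentence more plausibly belongs with the Kruskal-Wallis test for skewed data than with the primary proportions. It is redundant with two arms, but it changes no primary conclusion.

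**Conclusion.** The point holds as an ambiguity in the primary significance threshold, and it should be fixed. A primary P value between 0.025 and 0.05 has no single reading in the document. The possible inflation is from about 5% to about 10% family-wise. This applies only if 0.05 is used for both outcomes and either one can support a claim; the 9.75% figure further assumes independent tests. PPC power is practically unaffected by the choice if 15% versus 10% is right, so the consequence is for type I error and interpretation, not feasibility. The missing sizing basis for mortality is a secondary remark: the article gives no rate from which power for that outcome could be judged.

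**What to change.** - State in the Statistical analysis section that PPC incidence and perioperative mortality are each tested at two-sided 0.025, whichever of χ² or Fisher's exact test is used.
- Limit the 0.05 sentence to all other analyses.
- Restate the sample-size α as 0.025 and rerun the calculation. On 15% versus 10% the requirement is 2409 with attrition, so the planned 6000 need not rise.
- Delete the Nemenyi sentence.
- Say that the trial is sized on PPC incidence only, and that mortality will be reported with its difference and confidence interval.

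The cost is wording in the protocol, carried into the analysis plan and the registry entry where they state the threshold. Recruitment and conduct are untouched. The article reports recruitment as ongoing, so the change should be made before any unblinded result is seen. Making mortality a secondary outcome and testing PPC incidence alone at 0.05 would also give a single rule. However, it would change a primary outcome during recruitment and remove the only multiplicity control in the text, which is a larger step than the ambiguity requires.

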## Discussion

A tremendous amount of geriatric surgeries are performed around the world [18]. For elderly people, PPCs are a prevalent and serious threat [19, 20]. Reducing the risk of PPCs has always been a complex question, and investigators have put great effort into studying this topic. Previous studies have looked into interventions including inspiratory muscle training [21], smoking intervention [12], and respiratory rehabilitation [22, 23] to reduce the incidence of PPCs. Regarding intraoperative management, it was reported that low-tidal-volume ventilation or PEEP is effective in the prevention of PPCs [24, 25]. However, the LAS VEGAS study [26] published in 2017 and the PROVHILO study [27] published in 2014 failed to show the same result. Likewise, studies on high-flow oxygen have also reached obscure conclusions [28, 29]. The use of the LMA was reported to be superior to ETI in prehospital emergency care [30, 31], but its influence on PPCs in surgical elderly people lacks clinical evidence [20]. Therefore, this study is much needed to help optimize intraoperative airway management in this population.

There are several noteworthy limitations of this study. Firstly, all participating centers are located in east China; therefore, one may not postulate that results from this study can be implemented directly to other places or populations. Secondly, the long-term follow-up results are mainly based on patients’ self-evaluated questionnaires, which potentially can add bias to the results of this study. Thirdly, we are unable to apply uniform treatment to all patients. The ventilation mode adopted during anesthesia, administration of analgesics, and the prophylactic use of antibiotics, anticholinergics, and steroids are decided according to clinicians’ best judgement and will be recorded for future subgroup analysis. Other potential confounding factors [20], including surgery type and duration, will also be evaluated during statistical analysis. Moreover, the LMA device has many different forms and configurations. In this study, it is unreasonable to designate a single type of LMA device, but the mode of LMA used will be recorded. Lastly, the patient is not blinded in this trial, because extubation criteria need to be met before the LMA or the ETI tube can be removed. Even though we will make sure that every participant is informed not to reveal his/her group allocation to assessors, there is still the risk of assessor unblinding. In such cases, the patient will be evaluated by another assessor.

With our multi-center, randomized, controlled study, we aim to evaluate the safety profile of LMA/ETI use and add to the knowledge pool of airway management in elderly patients. The findings from this study can be used to help with clinicians’ understanding of the issue and can be used in clinical settings when decisions need to be made.

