Geriatric patients often have limited mouth opening and cervical movement, poor cardiovascular tolerance, and altered pharmacokinetics. Under these circumstances [5], a laryngeal mask airway (LMA) is considered a good alternative to endotracheal intubation (ETI) because of its advantageous characteristics such as ease of insertion [13], less irritation to the airway, less reliance on muscle relaxant, and better patient comfort [14]. As a supraglottic airway device, however, it does not separate the trachea from the esophagus; therefore, the LMA is associated with higher incidence of aspiration of gastric contents, especially in susceptible patients with a history of gastroesophageal reflux disease [15]. Moreover, the LMA is not recommended for use in lengthy surgery, morbidly obese patients, or certain other types of surgeries in which more control of the breathing (e.g., heart, lung, and brain surgeries) [16] is required. Therefore, the LMA and ETI both have major roles in daily anesthetic practice, and their influences on PPCs under various circumstances are inevitable topics for question.

In contrast to the popularity of LMA or ETI usage in geriatric surgeries, research evidence about their effect on PPCs is scarce and incomprehensive. Our group published a retrospective single-center study that compared LMA and ETI use in geriatric patients who underwent elective abdominal surgery, and we found that, among those who were transferred into the intensive care unit (ICU), the LMA group was associated with lower incidence of atelectasis and pulmonary embolism [17]. To better clarify whether the use of LMA is superior to ETI for elderly surgical patients and provide sufficient evidence for clinical decision-making, we have designed the current large-scale, randomized, controlled clinical trial. Its rationale, design, and protocol will be described in this paper.

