### Secondary outcomes

Secondary outcomes include ease of intubation (number of intubation attempts, disturbance to the following gastric tube insertion), anesthetics consumption, treatment for PPCs, duration of surgery, anesthesia recovery time and performance, time of PPC onset, postanesthesia care unit (PACU) stay, ICU admission and stay, re-admission rate, in-hospital days, hospitalization cost, and patients’ satisfactory score.

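### Measured surgery duration and ventilation mode arise after allocation, so they should not be handled as confounders or ordinary subgroup factors for the LMA effect

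*Protocol article*

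**What the plan says.** Three parts of the protocol article bear on this point.

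- **Discussion (limitations).** On care that is not standardised: "The ventilation mode adopted during anesthesia, administration of analgesics, and the prophylactic use of antibiotics, anticholinergics, and steroids are decided according to clinicians" and their judgement, and these items "will be recorded for future subgroup analysis". The paragraph continues: "Other potential confounding factors [20], including surgery type and duration, will also be evaluated during statistical analysis".
- **Statistical analysis.** Proportions are compared by a chi-square or Fisher's exact test. Then: "A logistic regression model will be developed to detect any potential confounding factors". No covariates are listed, and nothing confines the model to baseline variables.
- **Secondary outcomes** (and the Abstract). The list includes "anesthetics consumption, treatment for PPCs, duration of surgery, anesthesia recovery time and performance, time of PPC onset". Duration of surgery is therefore also an endpoint.

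**The concern.** A confounder of the treatment comparison is a common cause of treatment and outcome. Randomisation removes such causes up to chance. A variable that takes its value after allocation, and that the arm may influence, is not one of them. If it lies on the path from device to PPC, adjusting for it takes out part of the effect the trial wants to measure. If it shares unmeasured causes with PPC, such as frailty or surgical difficulty, conditioning on it makes the arms unlike each other within its levels and can produce an association where there is none.

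The protocol gives duration both roles: an outcome that the arm may change, and a potential confounder of the arm's effect. A duration-adjusted odds ratio or a PPC comparison within a ventilation-mode subgroup, published as confounder-adjusted or as a subgroup effect of LMA, could then be read as randomised evidence when it is not.

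**Working it through.** **Step 1. When each variable takes its value.** The protocol gives no figure for this point, so the first check sets its sections side by side.

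| Variable | Role given | Timing in the protocol |
|---|---|---|
| Surgery type | potential confounder | baseline item (Data collection and follow-up); baseline data precede randomisation (Ethics issues) |
| Surgery duration | potential confounder and secondary outcome | recorded on the day of surgery |
| Ventilation mode | subgroup factor | recorded on the day of surgery; chosen by clinicians |
| Analgesics; prophylactic antibiotics, anticholinergics, steroids | subgroup factors | chosen by clinicians; timing relative to randomisation not given |

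The blinding section says caregivers cannot be blinded, and the Intervention section leaves anaesthetic management and drug use to site practitioners. Measured duration and ventilation mode therefore follow allocation and can respond to it. Surgery type does not have this problem. For the drugs, the point applies only to those given after randomisation.

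**Step 2. What adjusting for duration can do (assumed inputs).** Simulation of 1,000,000 patients per scenario, with A = arm (1 = LMA, 0 = ETI), U = an unmeasured risk factor and e = standard normal noise:

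- Duration: D = s·A + 0.7·U + 0.714·e. Its within-arm SD is √(0.49 + 0.51) ≈ 1, so s is the arm's shift in SD units.
- Scenario (a), no arm effect on PPC: logit P(PPC) = −2 + 0.7·U.
- Scenario (b), arm effect wholly through duration: logit P(PPC) = −2 + 0.7·D.

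The overall PPC rate was 12% to 14%. Odds ratios for the arm:

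| Shift s (SD) | (a) unadjusted | (a) adjusted for D | (b) unadjusted | (b) adjusted for D |
|---|---|---|---|---|
| 0 | 1.00 | 0.99 | 1.00 | 1.00 |
| −0.1 | 1.00 | 1.05 | 0.93 | 1.00 |
| −0.25 | 0.99 | 1.12 | 0.85 | 1.01 |
| −0.5 | 0.99 | 1.26 | 0.72 | 1.00 |

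In (a) adjustment creates an apparent harm. In (b) it erases a real benefit. With s = 0 nothing is distorted.

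**Step 3. What a ventilation-mode subgroup can do (assumed inputs).** Suppose no device effect, half the patients at 8% PPC risk and half at 22%, so 15% overall. All ETI patients have controlled ventilation. In the LMA arm, 70% of low-risk and 10% of high-risk patients breathe spontaneously.

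- LMA patients left in the controlled subgroup: low-risk 0.5 × 0.3 = 0.15; high-risk 0.5 × 0.9 = 0.45; together 0.60.
- PPC in that subgroup: (0.15 × 0.08 + 0.45 × 0.22)/0.60 = 18.5% LMA against 15.0% ETI, a spurious 3.5 points.
- Milder selection (50% and 30% spontaneous): (0.25 × 0.08 + 0.35 × 0.22)/0.60 = 16.2%, a spurious 1.2 points.

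**Step 4. Scale.** After 10% attrition, 3000 × 0.9 = 2700 remain per arm. The subgroup then has 0.60 × 2700 = 1620 LMA and 2700 ETI patients. The difference d above 15% detectable with 90% power at two-sided 0.05 solves

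d = 1.96·√[p̄(1−p̄)(1/1620 + 1/2700)] + 1.2816·√[p₁(1−p₁)/1620 + p₀(1−p₀)/2700],

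with p₀ = 0.15, p₁ = 0.15 + d and p̄ the weighted mean. The right-hand side is 0.0228 + 0.0152 at the solution, so d ≈ 0.038. The 3.5-point artefact is a little below the 3.8 points detectable in that subgroup. The 1.2-point artefact would reach significance about 18% of the time.

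**The case against.** The strongest reply is that little is firmly planned. The sentence on duration sits in a limitations paragraph and says evaluated, not adjusted for. The subgroup work is described as future. The logistic model names no covariates, so linking it to duration is an inference, and covariate lists are commonly left to an SAP. This stands as far as it goes: the missing covariate list is not the complaint. The complaint is that the article names specific post-allocation variables and gives them the wrong role, which a later document would have to undo.

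Four stronger readings are tempting, and the documents do not support them.

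- *The randomised comparison is broken.* It is not. The stated comparison of proportions is unadjusted, and nothing makes the regression or a subgroup the primary analysis.
- *All the listed drugs are intraoperative.* The article does not time them, and some prophylaxis could precede randomisation.
- *The protocol itself says LMA changes ventilation mode and these drugs.* The Background speaks of "less reliance on muscle relaxant", and muscle relaxants are not among the listed subgroup factors. Nor does any section say that the arm changes surgery duration. An effect on ventilation is plausible, but it is not stated.
- *The bias would exceed what the trial can detect.* The risks and selection rates in step 3 are invented for illustration, and even the stronger case falls short of the subgroup's detectable difference.

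**Conclusion.** The point holds for the secondary regression and subgroup analyses only. Measured surgery duration and ventilation mode, and any listed drug given after randomisation, are not confounders of a randomised comparison. Adjusting for them or subgrouping by them can hide or manufacture an LMA effect.

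This rests on the arm being able to influence these variables. That is open for ventilation mode, because clinicians who know the arm choose it. It cannot be ruled out for duration, because the protocol compares duration as an outcome. If the arm leaves them unchanged, this distortion does not arise. The size and direction of any bias cannot be derived from the documents, and the simulated and worked figures show mechanism only. The wording should be corrected before analysis, but the main unadjusted result does not depend on it.

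**What to change.** Amend the Statistical analysis section and the limitations paragraph, or settle the matter in the SAP, along these lines:

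- Covariates and subgroups for the treatment effect are restricted to variables fixed before randomisation: PPC risk score stratum, centre, planned surgery type, age, smoking and COPD.
- Subgroup effects are assessed by a treatment-by-subgroup interaction test.
- Measured surgery duration, ventilation mode and post-randomisation drug use are reported descriptively by arm.
- Any analysis that conditions on these later variables is labelled exploratory or mediation, and is not presented as confounder adjustment or as a randomised subgroup effect.
- The logistic model is described as a covariate-adjusted estimate of the treatment effect using the baseline variables above, in place of a search for confounders.

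The cost is wording only. The baseline data are already collected before randomisation, and the trial is still recruiting, so the change can be made ahead of any analysis.
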